## Abstract

**Background:**

Due to the lockdown linked to the COVID-19 pandemic, the French National Authority for Health has recommended reinforced follow-up of psychiatric patients, with particular attention to people over 65 years. Cross-sectional studies reported an increased risk of anxiety, depression, and suicide during this period. Older people with psychiatric disorders are at higher risk of developing severe COVID-19 and worsening their psychiatric symptoms.

**Objective:**

The main objective is to evaluate the link between coping strategies and the onset of post-traumatic stress disorder (PTSD) after lockdown. The secondary objective is to assess the psychological factors influencing lockdown experiences such as personality, attachment type, or coping strategies.

**Method/Design:**

this is a multicenter cohort study including 117 patients followed up by phone in two French geriatric psychiatry units. Sociodemographic variables, psychiatric diagnoses, lockdown conditions, coping strategies, anxiety, and depressive symptoms reported during the first lockdown will be collected retrospectively from the medical file. A first prospective assessment including personality traits, attachment type, and traumatic life events will be conducted at 12 months (T1). Follow-up visits assessing anxious-depressive symptoms and PTSD will be made 18 (T2) and 24 months (T3) after the first lockdown. The primary outcome measure is PTSD symptoms. Secondary outcomes measures are coping strategies, generalized anxiety, anxiety about the COVID-19 pandemic, and quality of life.

**Discussion:**

This study aims to determine if the type of coping strategies usually employed have an impact on the onset of PTSD after a lockdown period. It will also determine if these coping strategies are influenced by other factors such as sociodemographic variables, lockdown conditions, particular personality traits, attachment type, and traumatic life events. This study could help identify factors associated with a poorer experience of lockdowns and pandemic crisis in elderly patients followed in a psychiatric center, and guide support in future similar situations.

**Trial Registration:**

ClinicalTrials.gov: http://clinicaltrials.gov/show/NCT04760795, Registered 18 February 2021.

## Introduction

In December 2019, the World Health Organization (WHO) (1) reported a new coronavirus (SARS-CoV-2) that quickly became pandemic, leading worldwide countries to take drastic measures. From March 2020, in France (2) unprecedented measures have been voted to limit travel (3), prescribing social distancing and isolation. Thus, several factors could affect the population's mental health, including the lack of scientific data on coronavirus disease 2019 (COVID-19), 24-h news channels reporting daily death count, and the government's lack of visibility on lockdown measures.

The epidemic situation and the resulting measures being unprecedented, the psychological consequences are difficult to predict. Previous studies on the mental health of the population, on the impact of quarantine measures, have been carried out on epidemics such as the severe acute respiratory syndrome (SARS) in 2003, the H1N1 flu in 2009 and 2010, the Middle East Respiratory Syndrome (MERS) in 2012, or Ebola in 2014. A recent literature review showed that quarantine measures hurt mental health leading to Post-Traumatic Stress Disorder (PTSD) susceptible to last for months or even years after measures implementation [Brook et al., (4)]. Indeed, anxiety, depressive symptoms, and PTSD were reported in the general population more than 1 year after the Ebola epidemic in 2014 (5). Some factors might affect the negative impact of quarantine, among them: sociodemographic characteristics and lockdown conditions (6), insufficient access to necessities including medical supplies and regular medical care (7–9), a lack of clarity in the information provided by the public health authorities, and a quarantine period exceeding 10 days (10). At the beginning of 2020, the French population experienced issues with the supply of masks and a long lockdown duration. Additionally, factors such as the government's lack of visibility on lockdown measures and 24-h news channels reporting daily deaths count could have negatively affected the population's mental health.

Self-protective measures such as wearing a mask or social distancing could have increased the onset of some disorders such as compulsive hand washing and agoraphobia, as shown by previous studies (11). Other long-term effects could be observed. Regarding the current COVID-19 pandemic, previous cross-sectional studies showed an increase in anxiety symptoms and depression, higher alcohol consumption, or poorer psychological wellbeing (12, 13). An international population-based study (14) also reported that the lockdown experience was linked to higher risks of depression, PTSD, and suicide (15).

In this context, the elderly population with psychiatric disorders, who is already frailer, might have poorer psychic health. Indeed, from the beginning of the pandemic, older people were more susceptible to developing severe COVID-19 (16). In addition, the media underlined the fragility of this age group and speculated on the choices that could be made by the intensive care services to favor younger patients in case of saturation. Next, older adults being less familiar with recent technologies and less prone to use video screen communications, the limitation of outings worsened their social isolation. The lockdown also complicated their daily organization because they usually depend on their children or external help (17). Finally, they also experienced more financial precariousness, knowing that socio-economic conditions have been identified as a risk factor for psychological disorders after quarantine measures during previous epidemics (10).

For patients with psychiatric disorders, the risks of social isolation and financial precariousness are increased, as is the risk of medical comorbidities and particularly cardiovascular comorbidities (18), making them even more vulnerable to the virus. Moreover, the onset of PTSD is more frequent in a population with a prevalent psychiatric pathology (19); and a longitudinal study (20) showed that psychiatric history induced anger and anxiety symptoms several months after the end of quarantine. Finally, psychiatric history increased the risk of suicidal ideation during the COVID-19 pandemic (14).

The concept of “coping” was defined by the set of cognitive and behavioral efforts put in place to control, reduce or tolerate internal and external demands that threaten or overwhelm an individual's resources” (21). Two types of coping were distinguished: problem-focused coping which constitutes the efforts undertaken to confront the situation, and emotion-focused coping which aims to decrease the emotional distress related to the situation. A synthesis of studies carried out on the adjustment strategies reveals the third set of strategies: seeking social support (22). Indeed, according to the situation, social support could help to change the problem or emotional state.

Bruchon-Schweitzer identified two determinants of the coping type: dispositional factors (personality traits, beliefs, motivation) and contextual factors, related to the context (nature of the situation, its imminence, duration, ambiguity, frequency, intensity, and controllability). Certain personality traits from the “Big Five” model (23) might influence the coping type. Neuroticism is defined as emotional instability and a persistent trend of negative emotions and might be more often associated with emotion-focused strategies (24).

An individual's response to stress might be associated with the quality of relationships, particularly the attachment dimensions. On the one hand, the attachment type seems to condition the physiological response to stress and the level of stress perceived by individuals (25). On the other hand, the way to face stress is related to attachment: Ognibene and Collin (26) studied the coping strategies employed according to attachment type in young adults. They showed that individuals with a secure attachment type received more help from friends and family and sought more social support when facing a stressful situation. While individuals with a preoccupied attachment type sought social support and tended to use avoidance strategies. Individuals with fearful and dismissing attachment types were less prone to seek social support.

Previous studies on traumatic events showed that some strategies, particularly problem-focused and seeking social support, were more efficient to prevent psychological repercussions such as PTSD (27, 28).

To our knowledge, no study has investigated coping strategies in epidemic or lockdown situations.

The French Health Authority has recommended a follow-up of the older psychiatric patients during the lockdown period. It advocated maintaining and reinforcement of outpatient care services by favoring teleconsultation by video or phone (2).

The present study includes a population of older outpatients with psychiatric disorders followed-up by phone in French hospitals over the lockdown period.

According to previous studies, we think that: a/ Patients could experience severe anxiety symptoms during this period. This anxiety might last after lifting the lockdown restrictions. However, we hypothesize that individuals who implement problem-focused and social support-seeking coping strategies might be less anxious. Additionally, the type of coping strategies used could influence the onset of PTSD; b/ Factors such as lockdown conditions, personality traits, attachment type, and life events might affect the coping strategies.

The primary aim of the study is to investigate the link between coping strategies and the onset of PTSD after lockdown.

The secondary objectives are threefold: a/Identify the coping strategies used during the COVID-19 crisis and measure their efficiency on generalized anxiety and anxiety about the COVID-19 pandemic, b/Assess the factors which influence the coping strategies used usually and during the lockdown, especially the sociodemographic variables, the lockdown conditions, the type of personality, the attachment type, and the presence of traumatic life events, c/ Evaluate the impact of PTSD on quality of life.

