The “secure” subscale (S) consists of 5 items. The “secure” attachment type indicates that the individual has positive views of self and others. Others are generally assumed available and helpful if necessary.The “fearful” subscale (F) consists of 4 items. It indicates negative perceptions of self and others. Others are generally assumed not available.The “preoccupied” (P) subscale consists of 4 items. It indicates a negative view of self and a positive view of others. The individual has a sense of personal worthlessness in the eyes of others and the belief that others are not available or caring in case of need.The “dismissing” (D) subscale consists of 5 items. It relates to a high level of self-confidence and negative views of others. The individual has a sense of self-worth that one owes only to oneself and very negative expectations of others from whom one should, on the other hand, expect nothing.

Each item is rated on a 5-point Likert scale (1 = *not at all like me* to 5 = *very much like me*). The four combining scores allow calculating the scores of two latent dimensions: the “self-model” and the “others” model.

- The presence of traumatic life events will be collected. Patients will be asked if they experienced one or several traumatic life events.

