### Dependent Variables

- The primary endpoint will be PTSD, assessed using the original version of the PTSD checklist (PCL) (31). It focuses on symptoms related to a single traumatic event. The PCL is a standardized self-reported rating scale including 17 items assessing the intensity, in the last month, of 17 PTSD key symptoms. Each item uses a 5-point Likert scale ranging (from 1 = *not at all* to 5 = *extremely*). Scores consist of the total symptom severity (sum of all items going from 5 to 85) and scores of three subscales corresponding to 3 for three PTSD sub-syndromes: re-experiencing of the traumatic event, avoidance of trauma reminders, and hyperarousal.

The secondary endpoints will be:

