## Appendix

**Table A TA1:** Summary of follow-up data collection.

	**T0**	**T1**	**T2**	**T3**
	**Retrospective collection**	**First prospective**	**Second prospective**	**Last prospective**
	**(on patient's records)**	**collection**	**collection**	**collection**
**Moment/Actions**	**Between March 17th and May 10** ^th^ **, 2020**	**T0 + 12 months**	**T0 + 18 months**	**T0 + 24 months**
Diagnostics information	X			
Sociodemographic	X	X	X	X
Interview on living conditions	X	X	X	X
Depression				
Short GDS	X	X	X	X
GDS 15			X	X
DSM V criteria			X	X
Anxiety about the context (ordinal scale)	X	X	X^*^	X^*^
Subjective psychic health (ordinal scale)	X	X	X	X
Generalized anxiety (GAD-7)	X	X	X	X
Contextual Coping strategies (BRIEF COPE)	X	X	X	X^*^
Dispositional Coping strategies (BRIEF COPE)			X^*^	
Personality (BFI)		X		
Attachment type (RSQ)		X		
Traumatic life events		X		
Post-traumatic stress (PCL)			X	X
Quality of life (SF12)			X	X

* *To ask only if the virus is still circulating. The STERACOVID study, 2020-2022, France*.

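### The primary aim is onset of PTSD after lockdown, but a last-month PCL at 18 and 24 months with no earlier PTSD measure and no stated index event gives prevalence of PTSD symptoms

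*Protocol article*

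**What the plan says.** - **Aim.** Introduction: "The primary aim of the study is to investigate the link between coping strategies and the onset of PTSD after lockdown". The Objective in the Abstract and the Discussion also speak of onset.
- **Endpoint.** Dependent Variables: the PCL is a 17-item self-report "assessing the intensity, in the last month, of 17 PTSD key symptoms". Of its reference event the section says only: "It focuses on symptoms related to a single traumatic event".
- **Timing.** Abstract, Method/Design: "Follow-up visits assessing anxious-depressive symptoms and PTSD will be made 18 (T2) and 24 months (T3) after the first lockdown". In Table A of the Appendix, the row that begins "Post-traumatic stress (PCL" is marked at T2 and T3 and is blank at T0 and T1.
- **Eligibility.** All patients have a psychiatric pathology. The Exclusion Criteria name major neurocognitive disorders and hospitalization, not prior PTSD.
- **Related data.** Psychiatric diagnoses come from the records at T0, where available (Inclusion Visit and Retrospective Data Collection), and the Discussion commits to using the ICD-10 diagnoses in the analyses. Traumatic events are asked once, at T1: "Patients will be asked if they experienced one or several traumatic life events".
- **Other wording of the endpoint.** The Abstract names PTSD symptoms as the primary outcome, and Sample Size gives 30% and 10% as expected prevalences.

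**The concern.** Onset needs either a population known to be free of the condition at the start or an outcome that dates the condition. The article gives neither. A last-month symptom score at 18 months shows who has symptoms then, not when they began or which event they concern.

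This matters beyond wording because the study wants to say which coping strategies protect against PTSD after a lockdown. The Introduction itself hypothesizes that life events affect coping. Trauma before lockdown could therefore be related both to coping style and to a positive PCL. If background PTSD is equally common in both coping groups, it pulls the association towards the null. If it is unequally common, it can produce an association with no effect on new PTSD.

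**Working it through.** **1. Can the planned data separate new from earlier or unrelated PTSD?**

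- A PTSD diagnosis already in the chart is visible at T0 if the record holds it. No stated rule removes such patients or analyses them apart.
- Unrecorded prior PTSD is not visible: no PTSD scale is scheduled at T0 or T1.
- PTSD from another event, before or after lockdown, is not separable: the article does not fix the PCL's reference event.
- Trauma history is known from T1, but the article does not say that events are dated. Statistical Analysis lists it as a correlate of coping and does not name it as a confounder of the PTSD model.

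The PCL result is thus the prevalence of PTSD symptoms, whatever their start or cause.

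**2. The plan's own figure.** Inputs from Sample Size: 30% vs 10%, two-sided 5%, 80% power.

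n per group = (1.960 + 0.842)² × (0.30×0.70 + 0.10×0.90) / (0.30 − 0.10)² = 7.849 × 0.30 / 0.04 = 58.87, rounded up to 59, so 118 in total.

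The stated figure reproduces. It is a calculation for a difference in prevalence.

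**3. Illustration of dilution.** The documents give no background rate, so q below is an assumption. Suppose 30% and 10% are onset risks and a share q of both groups has other PTSD. Then observed rate = q + (1 − q) × onset.

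| q | Observed rates | Odds ratio | Power, 59 per group (unpooled) |
|---|---|---|---|
| 0 | 30% vs 10% | 3.86 | 80% |
| 5% | 33.5% vs 14.5% | 2.97 | 70% |
| 10% | 37% vs 19% | 2.50 | 60% |
| 20% | 44% vs 28% | 2.02 | 45% |

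**4. The other reading of the same inputs.** If 30% and 10% already include background PTSD, as the word prevalence allows, nothing is added and the planned power for a prevalence comparison stands. With q = 5%, onset among those free of PTSD would be (0.30 − 0.05)/0.95 = 26.3% vs (0.10 − 0.05)/0.95 = 5.3%. The onset odds ratio would be (0.25/0.70)/(0.05/0.90) = 6.43, against 3.86 for prevalence. The prevalence odds ratio again differs from the onset odds ratio, but power is not lost.

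**5. Illustration of confounding.** No effect of coping on onset, unequal background, no adjustment, 59 per group:

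- Onset 10% in both, background 10% vs 5%: 19% vs 14.5%, OR 1.38, test significant about 10% of the time.
- Onset 20% in both, background 15% vs 5%: 32% vs 24%, OR 1.49, significant about 16% of the time (z = 0.08/√[(0.32×0.68 + 0.24×0.76)/59] = 0.97).
- Onset 10% in both, background 20% vs 5%: 28% vs 14.5%, OR 2.29, significant about 43% of the time.

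These splits are invented to show direction and scale.

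**The case against.** The plan is not blind to prior illness. Patients are regularly followed in psychiatric units, so a recognized PTSD diagnosis should be in the chart. The Discussion promises to use the diagnoses, and Statistical Analysis plans multivariate models with psychiatric factors. A case-definition rule could sit in an SAP, and the PCL's instruction line in the full protocol. The Abstract and Sample Size already describe symptoms and prevalence, so what is left may be one loose word.

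Much of this stands. The charted part of the problem is mitigated, and the missing index-event instruction would be a weak point taken alone. What does not fall away is that the visit schedule and eligibility are fixed in this article. An SAP cannot recover an earlier PTSD measure that was never taken, and chart diagnoses do not reach unrecorded PTSD or PTSD from another event. The word onset also recurs in the aim, the Abstract and the Discussion, and so shapes the conclusions.

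A reader might go further and infer that the plan has a rule classing all pre-existing PTSD as onset, that power is really 60 to 70%, or that any association found would be spurious. The documents do not support these. No such rule is written. The power figures require reading expected prevalence as pure onset. The spurious associations rest on assumed splits and on no adjustment. Nor does the statement that "the onset of PTSD is more frequent in a population with a prevalent psychiatric pathology" show that prior PTSD is common here: it concerns the risk of new PTSD.

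**Conclusion.** The concern holds as a mismatch between aim and endpoint. As written, the study estimates the association of coping with prevalent PTSD symptoms at 18 and 24 months. It cannot support a statement about onset after lockdown. T0 diagnoses and the T1 trauma item reduce the gap without closing it. The remaining gap is unrecorded prior PTSD and PTSD tied to another event.

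The effect on the coping association cannot be quantified from the documents. It may be dilution or confounding, and its size depends on a background rate that is not given and on whether 30% vs 10% already contains it. An assumed 5% equal background costs about ten points of power under one reading and none under the other. The sample-size arithmetic is not at fault.

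**What to change.** 1. Restate the primary aim and the conclusions as the association of coping with PTSD symptoms (prevalence) at 18 and 24 months.
2. Anchor the PCL to the lockdown/COVID-19 period and record when a patient answers about another event.
3. Exclude patients with a T0 chart diagnosis of PTSD from any analysis labelled onset, or analyse them separately.
4. For each traumatic event reported at T1, ask whether it came before or after March 2020, and adjust the PTSD model for pre-lockdown trauma.

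Two other remedies may suggest themselves and are not advised. A PCL at T1 would come 12 months after lockdown, so it cannot tell pre-lockdown PTSD from post-lockdown PTSD, and removing T1 cases could discard the cases of interest. Defining onset as a T3 case who was a non-case at T2 captures only PTSD arising between 18 and 24 months and misses everything earlier.

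The cost is one instruction line, one sub-question, a wording change, and a few patients leaving any analysis labelled onset. Even with items 2 to 4, unrecorded prior PTSD cannot be ruled out, which is why item 1 is needed in any case.

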## Methods and Analysis

### Study Design

It is a bicentric observational prospective cohort study. Figure 1 displays the typical schedule for a patient enrolled in the STERACOVID protocol.

**Figure 1 F1:**
[figure not shown]
The typical schedule for a patient enrolled in the STERACOVID protocol: a summary of the distinct stages.

### Setting and Patients

The STERACOVID study participants will be recruited among outpatients followed up by phone for psychiatric diseases during the lockdown related to COVID-19 in the geriatrics department of the University Hospital of Saint-Etienne and the aging psychiatric department of the Vinatier Hospital, Lyon, France.

#### Inclusion Criteria

Patients must: (1) be outpatient with a psychiatric pathology; (2) be 60+; (3) regularly followed in the psychiatric unit; (4) be followed by teleconsultation during the first lockdown due to COVID-19; (5) be affiliated or entitled to a social security scheme.

#### Exclusion Criteria

Patients with major neurocognitive disorders or hospitalized were excluded from the study.

### Study Withdrawals

Patients withdraw from the study in case of refusal or inability to continue the study for medical reasons. They will not be replaced. Patients will be followed-up as part of their usual care with no substitution treatment.

### Independent Variables

Independent variables will be:

- Sociodemographic characteristics will be collected: Age in years, sex (male/female), and marital status (single/in couple/widowed/divorced). For education, low and high educational levels are defined by the duration of schooling, with a threshold of 12 years (≥12 years vs. <12 years).- Information on lockdown period: total lockdown without outings (yes/no); social network (maintaining family contact, professional help visits); isolation (does the patient live alone at home?); feeling of loneliness (never/sometimes/often/very often); adoption of protective measures (yes/no); diagnosis of COVID-19 for the patient and/or in the close circle (yes/no); bereavement due to COVID-19; feeling about vaccine (willing to get vaccinated (yes/no/doesn't know/already vaccinated), reception of the announcement of a vaccine (reassured/indifferent/other)); obsessive thoughts of contamination (yes/no); presence and frequency of episodes of panic attack; worry (about oneself, relatives and/or the future); suicidal ideations (yes/no); delusional syndrome eventually linked to the lockdown (yes/no); the past time in watching TV news (0 h/ <1 h/1–3 h/more than 3 h), presence of daily routine (yes/no); information on tobacco and alcohol consumption, and sleep disorders (if yes, increased/stable/decreased), information on pain (type, duration, onset, daily interference, daily analgesic medication).- The personality will be assessed using the Big Five Inventory (BFI) (29). Built-in English, this self-report inventory has been validated in French and includes 45 items designed to measure the 5 dimensions of personality: openness (open-mindedness, originality), conscientiousness (control, goal-directed behaviors), extraversion (energy, enthusiasm), agreeableness (affection, altruism), and neuroticism (negative mood, anxiety). Each item consists of a short phrase and is rated on a 5-point Likert scale (1 = *disagree a lot* to 5 = *agree a lot* Scale scores are the sum of the items for each subscale.- The attachment type will be evaluated using the Relationship Scales Questionnaire (RSQ) (30). It is a self-reported multidimensional questionnaire including 30 items among which 17 items are specific to relationships and resulting in 4 subscales defining 4 attachment prototypes:

The “secure” subscale (S) consists of 5 items. The “secure” attachment type indicates that the individual has positive views of self and others. Others are generally assumed available and helpful if necessary.The “fearful” subscale (F) consists of 4 items. It indicates negative perceptions of self and others. Others are generally assumed not available.The “preoccupied” (P) subscale consists of 4 items. It indicates a negative view of self and a positive view of others. The individual has a sense of personal worthlessness in the eyes of others and the belief that others are not available or caring in case of need.The “dismissing” (D) subscale consists of 5 items. It relates to a high level of self-confidence and negative views of others. The individual has a sense of self-worth that one owes only to oneself and very negative expectations of others from whom one should, on the other hand, expect nothing.

Each item is rated on a 5-point Likert scale (1 = *not at all like me* to 5 = *very much like me*). The four combining scores allow calculating the scores of two latent dimensions: the “self-model” and the “others” model.

- The presence of traumatic life events will be collected. Patients will be asked if they experienced one or several traumatic life events.

